### **5.12 Criteria for discontinuation of research drugs or exit of this trial**

If any of the following occurs, the subject must stop the research drug:

1. Occurrence of treatment-related AEs that meet the discontinuation criteria specified in the study protocol.
2. Disease progression (subjects who meet the criteria for medication after disease progression can continue to be treated until the radiological evaluation confirms the progression and rules out the possibility of false progression).
3. During the study period, subjects receiving any prohibited combined treatments that affect the judgment of safety and efficacy can be required to stop the research drug after determined by the investigator and the sponsor's medical monitor.
4. Any intermittent disease that prevents the subject from continuing to receive research drug treatment.
5. The female subject is pregnant.
6. If the subject or his/her guardian is unwilling to continue the clinical research, he/she can propose to the doctor in charge at any time and discontinue the research drug immediately. According to the Declaration of Helsinki and other applicable laws and regulations, subjects have the right to withdraw from this

study at any time for any reason, and doctors or research centers must not be prejudiced in their future medical care.

7. Subjects who have poor compliance and fail to take medications on time and in amounts, when communication and coordination by the investigator is ineffective, or may cause significant deviations in the test results which cannot be remedied, can be determined to discontinue the research drug by the investigators.
8. Other situations where the investigator considers inappropriate to continue medication. Under any condition, the primary reason for discontinuing the research drug should be recorded in the original medical record. If the subject discontinues the research drug for any reason, for subjects who have received at least one research drug, the investigator shall make every effort to persuade the subject to accept the termination visit, and should continue to follow up those subjects with unresolved AEs.

### **5.13 Criteria for discontinuation of study drugs**

If any of the following adverse events related to the study drug occur, the administration of research drug should be permanently discontinued:

1. Grade 3-4 pneumonia;
2. Grade 3-4 hepatitis (elevation of ALT, AST or total bilirubin);
3. Grade 3-4 decrease of cardiac function;
4. Grade 3-4 pancreatitis;
5. Grade 3-4 allergic reactions;

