### **3. Study Design**

#### **3.1 Overall Study design**

This is a phase Ib/II study including dose exploration, followed by the multi-center, open-label extended study.

The dose exploration of the Phase Ib study, a standard “3+3” design was utilized to identify the maximum tolerated dose (MTD), dose limited toxicities (DLTs) and recommended Phase II dosage (RP2D) of chidamide in combination with sintilimab. Once the MTD, DLT and RP2D of Chidamide is determined, the Phase II study shall begin.

The phase II study is proceeded according to the RP2D of chidamide. Patients that achieved CR and PR could receive for up to one-year treatment, otherwise until disease progression, death, intolerable toxicity, completion of the scheduled treatment cycle, or the investigators' decision to withdraw (whichever occurs first). After 12 months, patients still with CR or PR were allowed to choose to continue or end of treatment or accepted autologous hematopoietic stem cell transplantation (ASCT) as consolidation (Stem cell mobilization, collection, reinfusion, conditioning regimen prior to autologous hematopoietic stem cell transplantation followed the medical routine at each study site). If patients choose to continue sintilimab plus chidamide, doses of chidamide reduce to 20mg twice a week and fixed doses of 200mg sintilimab intravenously every 30 days. Dose interruptions were allowed for treatment-related adverse events until these events resolved to grade 0–1 or to baseline level. Treatment was permanently discontinued for patients who had interruptions of more than 4 weeks. Patients will be visited for end of treatment within 4 weeks after the end of the study. For those whose condition is stable or improved after treatment, progression-free survival (PFS) follow-up will be carried out 8 weeks after the last administration of the study drug, and

continued every 12 weeks thereafter until disease progression, death, withdrawal of informed consent (ICF), receiving other novel treatments, or termination of the entire study (whichever occurs first). At the same time, patients who have developed PD will be followed up for overall survival (OS) every 12 weeks until death, withdrawal of ICF, or the termination of the entire study (whichever occurs first). The survival follow-up is conducted every 8 weeks for patients with disease progression.

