### 5.5 Dose adjustment

If any of the following conditions occurs, the dose of the research drug needs to be reduced in the next treatment cycle:

- Grade 4 hematotoxicity once
- Grade 3 hematotoxicity twice
- Grade 3 non-hematological toxicity once (except for alopecia).

During the combined treatment, chidamide is mainly adjusted according to hematotoxicity and non- hematotoxicity. Chidamide is reduced by 5 mg each time, and the dose could be reduced twice at most. (The standard of dose reduction is shown in the table below).

| Study Drug | Initial Dosage | First Reduction | Second Reduction |
|------------|----------------|-----------------|------------------|
| Chidamide  | RP2D (eg 30mg) | 25mg            | 20mg             |

The dose of sintilimab is not allowed to be adjusted during the entire study. The principles of suspension and permanent discontinuation of Sintilimab are shown in the Table1 below.

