| Type 1 diabetes       | Grade 3 hyperglycemia                                                                                                          | suspension b                |
|                       | Grade 4 hyperglycemia                                                                                                          | permanent discontinuation              |
| Renal insufficiency   | Grade 2 or 3 Elevated creatinine                                                                                               | suspension a                |
|                       | Grade 4 Elevated creatinine                                                                                                    | permanent discontinuation              |
| Neurotoxicity         | Grade 2 neurotoxicity                                                                                                          | suspension a                |
|                       | Grade 3 or 4 neurotoxicity                                                                                                     | permanent discontinuation              |
| Other AEs             | First appearance of other Grade 3 AEs                                                                                          | suspension a                |
|                       | Recurrence of the same Grade 3 AE                                                                                              | permanent discontinuation              |
|                       | Grade 3 AE: Failure to decrease to Grade 0-2/baseline level within 7 days or return to Grade 0-1/baseline level within 14 days | permanent discontinuation              |
|                       | Grade 4 AE                                                                                                                     | permanent discontinuation c |

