**Note**

a: Resume the administration after the symptoms improvement to grade 0-1 or baseline level.

b: For hypophysitis, adrenal insufficiency, thyroid insufficiency/hypothyroidism, and type 1 diabetes, resume the administration if they are fully controlled and only need physiological hormone replacement therapy.

c: For abnormal grade 4 laboratory test results, the decision whether to terminate the medication should be determined based on the accompanied clinical symptoms or signs and the clinical judgment of the investigator.

The maximum interval allowed for drug suspension is 12-weeks. If it is not possible to recover to the state where sintilimab can be reused within 12 weeks, the subject will be permanently suspended for sintilimab administration and then enter the follow-up phase. Except for the following two cases:

- Due to the application of glucocorticoids for the treatment of irAE, sintilimab was suspended for more than 12 weeks during the process of glucocorticoid reduction. Under this condition, it is necessary to discuss with the sponsor to decide whether to continue sintilimab treatment. The radiological examination for efficacy evaluation is still carried out as planned and is not affected by the suspension of medication.
- Due to treatment of AEs unrelated to sintilimab, it was suspended for more than 12 weeks. Under this condition, it is necessary to discuss with the sponsor to decide whether to continue sintilimab treatment. The radiological examination for efficacy evaluation is still carried out as planned and is not affected by the suspension of medication.

At the beginning of each treatment course, all hematological and non-hematological toxicities must be restored to no more than Grade 1 or the baseline level and the investigator considers it appropriate to proceed to the next course. If this condition is ineligible, the administration can be extended for 14 days. Once it's over 14 days, the investigator will decide whether the patient needs to withdraw from the study based on the risk-benefit ratio.

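### Section 5.13 permanently stops treatment for a related grade 3 pancreatitis or cardiac-function decrease, but Table 1 has no row for either and lets sintilimab resume after prompt recovery

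*Protocol*

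**What the plan says.** Section 5.13, headed "Criteria for discontinuation of study drugs", lists five related events at grade 3-4: pneumonia, hepatitis, decrease of cardiac function, pancreatitis and allergic reactions. If one occurs, "the administration of research drug should be permanently discontinued". Section 5.12 item 1 makes it mandatory to stop when a treatment-related event meets the protocol's discontinuation criteria.

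Section 5.5 gives Table 1 the same job for sintilimab: "The principles of suspension and permanent discontinuation of Sintilimab are shown in the Table1 below". Table 1 has rows for named toxicities and a residual Other AEs group. In that group, "First appearance of other Grade 3 AEs" leads to suspension under note a, which reads: "Resume the administration after the symptoms improvement to grade 0-1 or baseline level". A grade 3 event in this group becomes a permanent stop if it recurs or if recovery is slow: "Failure to decrease to Grade 0-2/baseline level within 7 days or return to Grade 0-1/baseline level within 14 days". Grade 4 is a permanent stop, with investigator discretion for laboratory results (note c). Before any new course, section 5.5 also requires that toxicities are at grade 1 or below, or at baseline, and that "the investigator considers it appropriate to proceed to the next course".

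For chidamide, section 5.5 calls for a lower dose in the next cycle after one grade 3 non-hematological toxicity, with alopecia the only exception. Section 5.9 calls for suspension and symptomatic treatment.

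**The concern.** Table 1 has no row for pancreatitis or cardiac function. A first grade 3 event of either kind, judged related to sintilimab, therefore gets two answers: no further dose under 5.13, and suspend then resume under Table 1. Neither 5.5 nor 5.9 refers to 5.13. Table 1 also repeats some of the 5.13 stops, such as grade 3-4 pneumonia, so it looks complete and gives a site no prompt to read further.

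What is at stake is patient safety and consistent conduct across centers. A patient could be given sintilimab again after an organ toxicity that the protocol's own list treats as a permanent stop, and two sites could handle the same event differently. Pancreatitis is foreseeable: section 5.3 names it among the grade 3 and above reactions seen with sintilimab monotherapy. That list does not name a decline in cardiac function, so the same cannot be said of the cardiac event from that source.

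**Working it through.** No figure in the plan needs reproducing. The check sets the rules side by side and then asks whether re-dosing could occur within the protocol's own timetable.

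**Step 1. First related event, rule against rule (sintilimab).**

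| Event | 5.13 | Table 1 (5.5) or Table 2 (5.6) | Agreement |
|---|---|---|---|
| Grade 3 pneumonia | permanent stop | own row: permanent stop | yes |
| Grade 3 hepatitis, normal baseline | permanent stop | own row: permanent stop | yes |
| Grade 3 hepatitis, baseline above ULN | permanent stop | own row: permanent stop only if it lasts over 7 days; no action given for a shorter rise | gap in Table 1 |
| Grade 3 allergic (infusion) reaction | permanent stop | Table 2: permanent stop | yes |
| Grade 3 pancreatitis | permanent stop | no row; Other AEs: suspend, then resume | **no** |
| Grade 3 decrease of cardiac function | permanent stop | no row; Other AEs: suspend, then resume | **no** |
| Grade 4 pancreatitis or cardiac decrease | permanent stop | Other AEs: permanent stop | yes, apart from note c |

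The direct conflict is two event types at one grade.

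**Step 2. Can Table 1 lead to a dose?** Inputs: a 21-day cycle; a permitted delay of 14 days (5.5 and 6.2 item 12); Table 1 recovery limits of 7 days (to grade 0-2 or baseline) and 14 days (to grade 0-1 or baseline).

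- Dose on day 1; next dose on day 1 + 21 = 22; latest delayed dose on day 22 + 14 = 36.
- For onset on day d, the limits fall on days d + 7 and d + 14.
- d = 7: days 14 and 21. Since 21 < 22, sintilimab could be given on schedule.
- d = 21: days 28 and 35. Since 35 < 36, it could be given within the permitted delay.
- In general, d ≤ 21 gives d + 14 ≤ 35 < 36.

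So a first grade 3 event starting on any of days 1 to 21 that meets both limits can be followed by another dose under Table 1, if the investigator considers the next course appropriate. Section 5.13 allows none. These timings are illustrations, not data.

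**Step 3. Chidamide.** With the 30 mg that 5.5 uses as its example of the recommended phase II dose, one grade 3 non-hematological toxicity leads to 30 − 5 = 25 mg in the next cycle. Section 5.5 exempts alopecia but not the 5.13 events. For a chidamide-related pancreatitis or cardiac event, the general rule therefore says reduce while 5.13 says stop.

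**Step 4. Which drug does 5.13 stop?** Its heading is plural, but its operative sentence speaks of the drug in the singular. Sintilimab stops for a sintilimab-related event, and chidamide for a chidamide-related one, on either reading. Whether the other drug also stops is not settled.

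**The case against.** The strongest reply is that the protocol already answers the question. Section 5.12 says that the drug must stop if any listed condition occurs, and its first item is meeting the protocol's discontinuation criteria. Section 5.13, which follows directly, names both events. A specific list normally prevails over a residual row, and resumption under Table 1 is not automatic because the investigator must agree to the next course. Most of this stands: 5.13 is the better reading. It does not remove the problem, because Table 1 is itself a set of discontinuation criteria, 5.5 names it as the source for sintilimab, and nothing there refers to 5.13.

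Several stronger readings are tempting, and the documents do not support them:

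- A reader might infer three contradictory chidamide instructions. Suspension in 5.9 and reduction in 5.5 can be successive steps (hold now, resume lower), and 5.9 states no resume rule for grade 3 non-hematological events. Only the 5.5 reduction pulls against 5.13.
- A reader might infer that 5.13 stops both drugs. That rests on the plural heading alone.
- A reader might count section 3.1 as a further conflict, since it says "Dose interruptions were allowed for treatment-related adverse events until these events resolved to" grade 0-1 or baseline. This is permissive overview text and does not require re-dosing after a 5.13 event.
- A reader might take the hepatitis duration condition as permission to re-dose. For a shorter grade 3-4 rise from a raised baseline, Table 1 gives no action, so 5.13 is the only stated one.

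**Conclusion.** The point holds in a narrow form. For a first sintilimab-related grade 3 pancreatitis or grade 3 decrease of cardiac function, 5.13 read with 5.12 item 1 requires a permanent stop, while Table 1 as written lets sintilimab resume after prompt recovery. The chidamide reduction rule in 5.5 likewise lacks an exception for 5.13 events.

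This rests on two assumptions: that an event without its own Table 1 row belongs under Other AEs, and that recovery meets both time limits. It would be too strong to say that the protocol authorizes re-dosing or leaves precedence wholly open. The fault is an unaligned table that a site could follow in good faith. The document gives no separate rate for either event, so the number of patients affected cannot be estimated. No effect on the primary endpoint or sample size is claimed. The change should be made because it concerns safety and costs almost nothing.

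**What to change.** - Add two rows to Table 1, pancreatitis and decreased cardiac function, each with permanent discontinuation at grade 3-4.
- State in 5.5 and 5.9 that the 5.13 list overrides the general reduce, suspend and resume rules.
- State in 5.13 whether the stop applies to the causally related drug or to both. This is a clinical decision for the sponsor, not a wording correction.
- Optional tidying: bring the Table 1 duration condition for grade 3-4 hepatitis with raised baseline into line with 5.13.

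The cost is protocol wording: two table rows and a few sentences. The downside is that a few patients who recover quickly lose the option of re-treatment, which 5.13 already denies them.

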### **5.14 Treatment compliance**

Patients will receive study drug treatment at the research center, under the close medical supervision of the investigator or authorized representative on the first day of

each cycle. Therefore, compliance assessment will not be performed.

## **6 Study progress**

### **6.1 Screening period (Day -28 to Day 0)**

Before starting any research-specific evaluation and operation, a written informed consent signed by the subject must be obtained.

A complete medical history should be recorded during screening:

1. Demographic data: including date of birth, gender, race/ethnicity; drinking history, smoking history.
2. Past medical history (except for this indication, including all past medical histories relevant to this study before signing the informed consent).
3. Past tumor history: including the date of diagnosis of the tumor, the start/end date of the previous treatment plan, the best treatment evaluation, and the date of disease progression; the radiotherapy history should include the start/end date and the location of the radiotherapy. Previous valuable operations (such as gastroscopy, needle biopsy and other diagnostic or therapeutic invasive operations) need to be recorded in the eCRF, including the start/end dates, the name and location of the operation.
4. Vital signs: including blood pressure, heart rate, respiration rate, body temperature. Blood pressure should be measured after the patient rests for 5 minutes.
5. Physical examination: including height (only for screening), weight, head, eyes, ears, nose, throat, neck, heart, chest (including lungs), abdomen, limbs, skin, lymph nodes, nervous system and general conditions of the patient.
6. ECOG score: It is recommended that the same researcher conduct ECOG evaluation during the entire study period. See Appendix II for details.

7. Laboratory examination: Specific laboratory examination indicators include hematology examination, blood biochemistry and urine examination.
  - a) Hematology examination: red blood cell count, hemoglobin, hematocrit, reticulocyte count, white blood cell count and classification (neutrophils, lymphocytes, eosinophils, monocytes, basophils and other cells) and platelet count as well.
  - b) Blood biochemical tests include total protein, albumin, blood sugar, total cholesterol, low-density lipoprotein, high-density lipoprotein, triglycerides, urea, creatinine, alkaline phosphatase, lactate dehydrogenase, total bilirubin, direct bilirubin, indirect bilirubin, AST, ALT, calcium, phosphorus, magnesium, potassium, sodium, chloride, serum amylase, uric acid.
  - c) Urine routine test includes specific gravity, pH, urine sugar, protein, cast, ketone and haemocytes. During the screening period, if urine protein examination is more than ++ or judged by the doctor as abnormal and clinically meaningful, 24-hour urine protein quantification and 24-hour urine creatinine determination are required.
8. Histopathological testing.
9. 12-lead electrocardiogram.
10. Cardiac ultrasound examination (including evaluation of left ventricular ejection function).
11. Thyroid function.
12. Pulmonary function.
13. Serum pregnancy test (if applicable);
14. Serum virology test: including hepatitis B markers, HBV-DNA, HCV, HIV.

15. Bone marrow examination (smear  $\pm$  biopsy).
16. Tumor evaluation: Assessed according to the RECIL 2017 lymphoma evaluation standard. See Appendix II. During the screening period, CT scan of the chest, abdomen and pelvis or PET/CT of whole body should be performed. If there are clinical indications, appropriate methods can be used to examine any other known or suspected locations of diseases, such as cranial MRI, bone scan.
17. Combined medication: Collect all medications during the screening period, including the generic name, the first dose, the reason for the medication, and the start and the end date of the medication.
18. Adverse events (AEs): AEs are collected during the screening period from the signing of the ICF until the first dose.
  - i. Laboratory tests, 12-lead ECG, echocardiography, serum pregnancy test (if applicable), and bone marrow examination should be completed during day -7 to day 0.

## **6.2 Visits during the treatment period**

1. Vital signs.
2. Physical examination.
3. Weight measurement.
4. Laboratory examination: Before each medication administration during the treatment period, the laboratory examination must be completed and the blood sampling time should not be earlier than 48 hours before the medication. Only when the investigator determined the laboratory examination results qualified can the subjects continue medication. During the treatment period, the investigator can increase the frequency of blood routine examinations

according to the conditions of the subjects.

5. Plasma EBV-DNA monitoring: Monitored on the first cycle of treatment and the first day of subsequent cycle. After all treatment courses are completed, monitored once a month at a fixed time.
6. 12-lead electrocardiogram: Evaluated every 3 weeks ( $\pm 3$  days) from the first administration.
7. Cardiac ultrasound examination (including evaluation of left ventricular ejection function): evaluation will be carried out every 12 weeks ( $\pm 7$  days) from the first administration.
8. Thyroid function: Evaluated every 3 weeks ( $\pm 3$  days) from the first administration.
9. Pulmonary function: Evaluated every 12 weeks ( $\pm 7$  days) from the first administration or there may be clinical needs.
10. Bone marrow examination (smear  $\pm$  biopsy): Evaluated every 6 weeks ( $\pm 7$  days) from the first administration for those with bone marrow infiltration or there may be clinical needs.
11. Tumor evaluation: Baseline and follow-up evaluations should adopt the same radiological methods and be performed by the same investigator as far as possible. Tumor assessment will be calculated according to the actual date of medication before each medication and will be evaluated every 6 weeks ( $-7$  days), regardless of the effect of drug withdrawal. For patients who are suspected of developing PD before the next scheduled evaluation, an extra tumor evaluation should be performed.
12. Administration of the research drug: Administered every 3 weeks. If the subject cannot take the medicine at the planned time due to special reasons

(such as adverse reactions), a maximum delay of 14 days is allowed.

13. Record the combined medication;

14. Record AE.

